**July 30, 2019**

**University of Michigan Version 1.5**

| **Study Title** | PLUS Where I Go Mobile Application |
| --- | --- |
| **Study Design** | Prospective observational |
| **Primary Objective** | To establish feasibility, acceptability of use, and the extent to which all questions are answered (data completeness) |
| **Secondary Objective(s)** |  |
| **Research Intervention(s)/Investigational Agents** | N/A |
| **IND/IDE # (if applicable)** | N/A |
| **Investigational Drug Services # (if applicable)** | N/A |
| **Study Population** | Adult English-speaking community women |
| **Sample Size** | N = 60 across sites  University of Michigan = 24; other sites = 12 each |
| **Study Duration for Individual Participants** | Two in person visits will last about 40-60 minutes. Actual use of Where I Go is estimated to take approximately one hour total across the consecutive 48 hours of its use. |

[I. Rationale and Background 4](#_Toc13582646)

[II. Objectives 5](#_Toc13582647)

[III. Specific Aims 5](#_Toc13582648)

[IV. METHODOLOGY 6](#_Toc13582649)

[A. Overview 6](#_Toc13582650)

[B. Instruments embedded in the “Where I Go” Application 6](#_Toc13582651)

[C. Recruitment 8](#_Toc13582652)

[D. Visit one 9](#_Toc13582653)

[E. Between visits (48 hours) 10](#_Toc13582654)

[F. Visit two 10](#_Toc13582655)

[Data Retention and/or Data Destruction Plan 10](#_Toc13582656)

[G. Statistical Considerations 13](#_Toc13582657)

[V. Expected Outcomes of the Study 14](#_Toc13582658)

[VI. Duration of the Project 14](#_Toc13582659)

[VII. Compensation 14](#_Toc13582660)

[VIII. Project Management 14](#_Toc13582661)

[IX. Risks and Benefits 15](#_Toc13582662)

[A. Risks 15](#_Toc13582663)

[B. Benefits 15](#_Toc13582664)

# **Rationale and Background**

Mobile/smart phones are used across diverse segments of the population and are a compelling vehicle for research data collection. According to the PEW Research Center, 77% of adults in the United States own a smartphone (2016) with the highest adoption rates seen primarily in adults with college degrees who are young and upper income earners. Smartphones offer unique opportunities to engage individuals and understand how the physical and social environment influences their health. Users typically carry their phones with them, interact with their phones multiple times each day (e.g. nearly 100 phone “touches” per day on average), and spend several hours per day engaged in activities that were once only possible on desktop or laptop computers (e.g. viewing, searching, messaging, gaming). Many phones also contain unobtrusive motion sensors, GPS-enabled time and location tagging, and up-to-the-minute phone and app usage statistics that can be used to characterize some aspects of an individual’s interactions with the physical and social environment.

As a result, the NIDDK-funded PLUS Consortium has chosen to investigate the utility of a Mobile Bladder Application to study bladder health in community women and girls. The **long-term goal** of a Mobile Bladder Application is to enhance our understanding of the wide variance in bladder habits in varied environments over time and to identify the underlying individual risk and protective factors, so we inform broad scale public health education on best practices for lifelong bladder health. Collecting data via the app will contribute information that supports the overall PLUS Consortium goals. These are to study the determinants of bladder health, identify risk factors for lower urinary tract symptoms and conduct prevention and interventional studies in women. The **short-term goals** are to 1) build a tool to measure bladder habits and special/temporal associations in women and 2) evaluate the ease of usability for participants.

The PLUS mobile bladder application called “Where I Go” is designed to be a technologically intensive data collection vehicle. The long-term goal is to use Where I Go in studies that aim to obtain a clearer picture of how bladder habits are related to factors in a woman’s environment (home, work, and public spaces). Baseline demographics will be collected prior to using the app. Once the app is downloaded, the woman will report bladder habits, environment and social factors over a 48 consecutive hour time period. This will allow us to study the associations between individual behaviors, environmental factors and ways in which women manage their bladders in day-to-day life. Additional to the woman’s environment (home, work and public spaces), Where I Go will offer the woman opportunities throughout her day to record her fluid intake, and toileting factors such as whether she is able to go to the bathroom on her own accord or is restricted in some way, what adaptive behaviors she has to make, and whether or not she has ready access to toileting.

# **Objectives**

The overarching goal of Where I Go Stage 3 development is to establish feasibility, acceptability of use, and the extent to which all questions are answered (data completeness). Our goal is to achieve user testing with approximately 60 English-speaking community women across sites, with 24 user testers at the University of Michigan. We anticipate that additional testing will be needed for a more broad representation.

# **Specific Aims**

**AIM 1: To measure the user’s experience (acceptability) of the app, and refine as indicated by results.**

Hypothesis 1.1: The System Usability Scale (SUS) for participants will show a mean raw score of 74 or greater.

Hypothesis 1.2: The Functionality subscale of the Mobile Application Rating Scale (MARS) for participants will show a mean score of be 3.5 (based on 1-5 scale).

**AIM 2: Analyze user response rates of a.) The real-time self-initiated Where I Go prototype 1 components and b.) Where I Go mobile application prompts.**

Hypothesis 2.1: For the “real-time” reporting portion of Where I Go, over 70% of voiding events that occur during the day will be entered as confirmed by total void events reported in the prompted portion of Where I Go.

**AIM 3: Explore key factors that influence decisions for revisions of the mobile bladder app (Qualitative Aim).**

Hypothesis 3.1: Using one-to-one interviews with participants after using the app, we will identify key factors related to the Where I Go that will inform refinements needed for the Where I Go revision prototype that follows.

**AIM 4: Data collected from the Where I Go is transferred, downloaded and can be used by Scientific Data Coordinating Center (SDCC) for analysis. The main goal of this aim is to test feasibility of data transfer, management and analysis.**

Hypothesis 4.1: SDCC will work with University of Michigan-Ann Arbor Center for Health Communications Research (CHCR) to safely download and accurately analyze the data collected from the Where I Go prototype 1 to answer questions in Aim 1-3 and other exploratory analyses.

# **METHODOLOGY**

## **Overview**

Stage 3 of Where I Go development will involve in-person contacts with a research coordinator at selected research sites from the Preventing Lower Urinary Symptoms (PLUS) consortium, including the University of Michigan site. Where I Go study participants will be observed for ease in following download instructions for the app on their iOS or Android device and will be assisted as needed, with documentation of problems. Similarly, participants will be given instructions on how to interact with the Where I Go app (prototype 1) for 48 consecutive hours, and feedback on ease of use will be obtained. A follow-up survey will include a validated usability survey and open-ended questions about using the app. Modifications from the study will be incorporated into the app development process resulting in a fully refined Where I Go prototype 2 available for future additional testing.

## **Instruments embedded in the “Where I Go” Application**

There are five modules in this study: demographics, real-time assessment, check-ins, feedback surveys, and a qualitative script. All are bundled as Where I Go application data (app data), with the exception of a qualitative script. The screen by screen shot shows onboarding knowledge how the app data will be used and stored on secure servers at the University of Michigan.

**App data: Demographics**

The app will ask participants to personalize the app by adding their nickname or whatever they want. The app will gather information on age, education, ethnicity, race, income, number of toilets in home, and daily wake up/sleep schedule.

**App data: Real-time assessment**

Participants will answer questions within the app. They will be asked to input the time and location/where they urinated, how strong their urge was to urinate, whether they had to delay urination, reasons for the delay, and reasons they urinated.

**App data: Check-ins (Ecological Momentary Assessments)**

Participants will be asked to input the time and location/where they urinated or leaked, environment around them, pain if any while urinating, amount of liquid they drank, type of liquid they drank as in any caffeine, artificial sweeteners or alcohol, and strategies they used to reduce their need to urinate.

**App data: Feedback Post surveys (SUS, MARS)**

The System Usability Scale (SUS) is a validated 10-item questionnaire with 5 response categories (strongly disagree to strongly agree) and self-administered. The SUS contains questions specific to the woman’s experience in using the app questions about when they use the app, if it is difficult or easy to use, needing help or not, liking the features in the app, understandability, learning the app quickly, and having confidence. It is the most widely used questionnaire for measuring the perception of usability. It was developed in 1986 and has been used to measure software, websites, cell-phones, hardware, interactive voice response systems, paper ballots and even the yellow pages. It has been cited in over 600 research applications.

The Mobile App Rating Scale-Functionality (MARS) consists of 4 question stems with 5 responses (1- inadequate, 2-poor, 3-acceptable, 4-good, 5-excellent). The functionality questions assess performance, ease of use, navigation and gestural design. It was developed in 2015 and is a simple, objective and reliable tool for participants to provide feedback on the quality of a mobile app such as Where I Go. The MARS had excellent internal consistency and excellent interrater reliability when used to rate 50 mental health and well-being apps. (Stoyan SR, Hides L, Kavanagh et al. Mobile App Rating Scale: A new Tool for Assessing the Quality of Health Mobile Apps. JMIR Mhealth Uhealth. 2015 Jan-Mar3 (1):e27).

An additional 4 questions ask if the check-in notification was bothersome, if the questions in the app were understandable, if the user would recommend the app to others and anything else they want to share with us.

**Qualitative script**

Qualitative script to obtain feedback from participants on their experience of using Where I Go, as organized by the following general categories. These categories will provide the beginning framework for later processing/collating comments. It is expected that collating will also be organized according to purposely chosen demographics, such as age groups, whether employed outside the home, rural or urban, education level, race, etc.

Participants will be asked their experiences with the Where I Go app and perceptions using the app, such as, their experience with the way the app worked, how they app looked, the information covered on the app, the ways that might improve the app, their perceptions using the app influenced their thought of bladder health and toileting behaviors, the overall quality of the app, aspects should be changed, anything else was not discussed and they wanted to share with us.

This study also includes paper-based questionnaires:

**Feedback Post surveys (SUS, MARS)**

Paper versions of the Feedback surveys will be available for use as needed. These are imbedded in the app under Post Survey.

**Socio-demographics**

Participants will be asked their marital status, home status, employment, health insurance, any bladder problems, income, education, language, race, gender, and romantic or sexual attraction.

**Health Survey**

Participants will be asked if they were diagnosed for some medical conditions such as diabetes, and asthma, if even pregnant or give birth, menstruating status, any treatment for bladder problems, using female hormones, taking diuretic medications, and height and weight.

**Lower Urinary Tract Symptoms**

Participants will be asked about their bladder behaviors such as number of pee during day or night, any urgency, frequency, amount of the leaks, bothersome of the leaks, and triggers for leaking pee.

**Where I Go Step by Step**

Coordinators will have a step-by-step guide to assist in study processes

1. Recruitment advertisements placed
2. Interested women contact research staff
3. Screening executed (screening ID assigned) Exit form completed for non-eligible women who are thanked for their interest
4. Eligible women are scheduled for in-person visit one
5. Each participant receives a reminder letter/call/email with date/time, informed consent, directions, parking permit

**TIME POINT 1 - Visit 1**

1. Research Coordinator reviews informed consent form, participant signs and is given a copy
2. Participant is assigned an access code and instructed through the next steps:
   1. Connect to wireless network
   2. Download and install Where I Go app on smartphone
   3. Personalize app with nickname
   4. Complete demographic questions in the app
   5. Complete study packet on paper
3. Schedule 2^nd^ visit which should occur after 48 consecutive hours and within two weeks
4. Payment processed for Visit 1 ($25)

**TIME POINT 2 – between visit 1 and 2**

1. Participant: Use Where I Go app for 48 consecutive hours (inputting data)
2. Coordinator: Check participant’s dashboard for completion of Post Surveys (SUS, MARS, Additional ques.)
3. Send reminder for completion of Post survey and 2nd visit by text/phone/email

**TIME POINT 3 - Visit 2**

1. Participant completes Post survey in app if not previously done (SUS, MARS, Additional ques.)
2. Qualitative interview (written notes while audio recording)
3. Remove the app from participant’s phone
4. Payment processed for app usage and Visit 2 ($75 + $50 = $125)
5. Participant involvement complete

| **RESEARCH STAFF ONLY** |
| --- |

1. REDCap entry for appropriate instruments
2. Qualitative interview notes and audio recording data stored (locked office, locked file cabinet PI research office)
3. Identified data (name, phone, email & address) electronically stored on secure password protected local area network, School of Nursing server/password protected folder/individual ID password file
4. Analysis
5. Send participants, who have not withdrawn, Pelvic Floor newsletter with information about presentations, manuscripts and new studies until participants requests to stop

## **Recruitment**

Assuming 20% dropout, we will recruit women across 4 sites: University of Michigan, Loyola University, University of Pennsylvania and University of Alabama at Birmingham. UM will recruit 24 with other sites recruiting 12 each. Community women will be recruited through an institution-based research volunteer website (umresearch.org) and with a newsletter (Pelvic Floor Newsletter). The newsletter will be sent to previously consented study participants who signed and marked yes on the informed consent section: *Consent to be Contacted for Participation in Future Research*. Interested women will contact the research staff and the initial screening will occur by phone using the Screening Script for Recruitment.

*Study inclusion and exclusion criteria*

Inclusion criteria:

- Female sex assigned at birth
- Age ≥ 18
- Fluent in written and spoken English
- Owns a smartphone (Android or iOS), able to make phone calls, and download at least one app in the past 6 months through the app store
- Willing to respond to Where I Go prompts/texts and input data about toileting behaviors for a consecutive 48 hours
- Have to leave home at least once during the 48 hour app usage period
- Agree to two in-person visits and to bring their smartphone to the School of Nursing
- Stand/walk independently without human assistance (cane permitted)
- Will not change time zone
- Willing to add locations, must include her home

Exclusion criteria:

- Physical or mental condition that would prohibit completion of written questionnaires and interaction with the bladder application
- Institutional living arrangement (i.e. skilled nursing, long term care or rehabilitation center)
- Currently pregnant (self-reported)
- Known neurogenic or congenital bladder condition
- Unable to use toilet independently
- Male sex assigned at birth

In addition to the above inclusion/exclusion criteria, effort will be made to recruit broadly across selected demographics, such as age groups, whether employed outside the home, rural or urban, education level, race, etc. During the screening call, a unique screening site ID will be assigned. The screening ID will allow us to tally screening failures. Those that are ineligible, the coordinator will complete the Where I Go Exit Form. To those eligible for the study, the first visit will be scheduled, and the informed consent, scheduling letter with parking permit will be mailed for review. Just prior to the first visit, eligible participants will receive a visit reminder by phone/email/text.

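### The protocol gives 60 women (24 at Michigan) both as the number recruited under 20% dropout and as the number in whom testing is to be achieved; if testing means completion, about 48 (about 19) are expected

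*Protocol*

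**What the plan says.** Three places in the protocol carry the sample size.

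- **Synopsis, Sample Size row:** "N = 60 across sites", split as 24 at Michigan and 12 at each other site. It does not say whether these are women enrolled or women completing.
- **Objectives:** "Our goal is to achieve user testing with approximately 60 English-speaking community women across sites, with 24 user testers at the University of Michigan". This is worded as something to be achieved.
- **Recruitment:** "Assuming 20% dropout, we will recruit women across 4 sites", followed by "UM will recruit 24 with other sites recruiting 12 each". This is worded as intake, with dropout still to come.

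No section gives a separate target for completers, and none gives a recruitment figure larger than 60. The protocol does not define dropout.

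**The concern.** A dropout assumption normally separates two numbers: how many are recruited and how many are expected to finish. Here one number serves for both. On the ordinary reading of the Objectives, either the 20% allowance was never applied, or it was applied to a completer target that the protocol does not state.

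This matters for two reasons. First, feasibility is part of the primary objective, so expected completion should be clear in advance. As written, 48 completers could be reported either as exactly what was planned or as a shortfall of one fifth. Second, a site cannot tell whether to stop at its stated number enrolled or to continue until that number has completed.

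**Working it through.** **Inputs, all from the protocol**

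- Dropout d = 20% (Recruitment).
- Recruited: 24 at Michigan and 12 at each of three other sites (Recruitment).
- User testing to be achieved: about 60 overall, 24 at Michigan (Objectives).
- Stated sample size: 60 (synopsis).

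**Step 1. Reproduce the stated size.** 24 + 3 x 12 = 60. This agrees with the synopsis and the Objectives, so the number recruited and the number to be achieved are the same.

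**Step 2. Completers expected from 60 recruited.** Completers = N x (1 - d).

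- Overall: 60 x 0.8 = 48
- Michigan: 24 x 0.8 = 19.2
- Each other site: 12 x 0.8 = 9.6
- Check: 19.2 + 3 x 9.6 = 48

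**Step 3. Recruitment needed for 60 completers.** N = n / (1 - d).

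- Overall: 60 / 0.8 = 75
- Michigan: 24 / 0.8 = 30
- Each other site: 12 / 0.8 = 15

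The cruder rule n x (1 + d) gives 60 x 1.2 = 72. Neither rule returns 60.

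**Step 4. Which target would make 60 a correctly inflated figure?** 48 / 0.8 = 60, or 50 x 1.2 = 60 by the cruder rule. The protocol states neither 48 nor 50.

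**Step 5. Which data does a woman who leaves early not supply?**

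- *Interview (Aim 3):* held only at visit two, so it needs attendance there.
- *SUS and MARS (Aim 1):* requested by the app's last query after the 48 hours, or completed at the start of visit two (Between visits). A woman who stops during the 48 hours would generally not supply them. A woman who misses only visit two still can.
- *Void entries and check-ins (Aim 2):* entered during the 48 hours, so a partial user may contribute some.

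The figure of 48 is therefore firmest for the interview, somewhat less firm for the surveys, and least firm for the void entries.

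**Step 6. Effect on precision.** The ratio of standard errors is sqrt(60/48) = 1.118, about 12% larger with 48. As an illustration only, take the SUS mean, for which the protocol gives no standard deviation. Assume a standard deviation of 15, with a range of 12 to 20, on the scale on which the threshold of 74 is expressed. The half-width of a 95% t-interval is t x SD / sqrt(n):

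| Assumed SD | n = 60 | n = 48 |
|---|---|---|
| 12 | 3.10 | 3.48 |
| 15 | 3.87 | 4.36 |
| 20 | 5.17 | 5.81 |

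At an SD of 15 the difference is about half a point.

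**The case against.** The strongest reply is that the sections can be reconciled. The Objectives speak of user testing and do not mention completers. Testing begins at visit one, where the coordinator observes the download and documents problems (Overview, Visit one). Compensation covers attempted as well as actual use. The data-usage estimate under Risks applies the term usability tester to an estimate that includes the download. If every woman who installs and tries the app is a tester, then 60 enrolled are 60 testers, of whom about 48 finish. The Recruitment sentence can also be read as an allowance already made, since 48 / 0.8 is exactly 60.

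Part of this stands. A reader might infer that the two figures cannot both hold on any reading; the documents do not support that, because user tester is undefined and the looser meaning is available. It is a strained meaning for Aims 1 and 3, however, whose data come after use of the app. Nor does the qualifier in "Our goal is to achieve user testing with approximately 60 English-speaking community women across sites" comfortably cover a 20% shortfall, and the phrase "with 24 user testers at the University of Michigan" carries no qualifier of its own. If the allowance was already made for 48, the arithmetic is sound, but the protocol still does not state that target.

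A reader might also infer that every result will rest on 48 women. Step 5 of the working shows otherwise. Finally, a reader might infer a loss of power. The protocol contains no power or precision calculation, and thresholds such as "The System Usability Scale (SUS) for participants will show a mean raw score of 74 or greater" are stated without reference to the number of women.

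**Conclusion.** The point holds in a conditional form. If user testing means completing the 48 hours, the post-survey and visit two, and if dropout is 20% as assumed and similar across sites, the plan yields about 48 completers and not 60: about 19 of 24 at Michigan and 9 to 10 of 12 at each other site. The protocol uses 60 for both roles and does not say which it means.

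The consequence is a headline number that is less favourable once it is stated as completers, with standard errors about 12% larger than 60 would give. The documents do not show a breached power or precision figure, a single denominator of 48 for all aims, or a need to recruit 75. The last would follow only if 60 completers were truly intended, which the protocol does not establish. It is worth correcting because feasibility is part of the primary objective and the correction is cheap.

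**What to change.** Restate the sample size in the same terms in the synopsis, the Objectives and Recruitment. Suggested wording: *Sixty women will be enrolled (24 at the University of Michigan and 12 at each of three other sites). With 20% dropout, about 48 (about 19 at Michigan and 9 to 10 at each other site) are expected to complete the 48 hours of app use, the post-survey and visit two.*

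Report each aim with its own denominator: women with void entries for Aim 2, women with SUS and MARS for Aim 1, and women interviewed for Aim 3.

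The cost is a change of wording in three places and a less favourable stated number of completers. Enrolment, procedures and site allocations stay as they are.
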